### The study intervention

The purpose of the rehabilitation program is to provide a personalized approach that allows the patient to develop knowledge and understanding of the disease and to maintain or develop the necessary resources and abilities to manage their life situation.

The stages of the study intervention are described below and include: initial screening; clinical examination prior to inclusion; randomization; a preparation day; four-week hospitalization; six and twelve months follow-up.

### Initial study screening

Patients referred to the hospitals are routinely sent a brief health screening questionnaire that upon return is assessed by the admission nurse to exclude patients who have a dependency level requiring intensive care and thus lack the rehabilitation potential defined by the inclusion criteria (equivalent to a EDSS score >7.5). The screening includes two basic models: factor evaluation and prototype evaluation, and includes assessment of physical and cognitive function/limitations (modified Barthel-100 index) [12-14]. The screening can be conducted as a home visit if necessary. Proposals for patient exclusion from the study will be discussed with a neurologist. The initial screening does not exclude wheelchair users or patients who need help from others to complete the questionnaire.

### Clinical examination prior to study inclusion

Patients who fulfill the initial screening criteria will receive by ordinary mail a study information pack including detailed information about the study and patients’ rights in a health science research project. Patients willing to participate in the study should respond within 10 days by phone or mail.

Potential participants will be invited to an ambulatory consultation with a neurologist. The consultation will include standard neurological examination, screening for severe depression [15] and a walking test. The neurologist completes a screening form covering information about the patient's previous and current medical treatment and information relevant to the in- and exclusion criteria. Patients will receive additional oral information about the study and a final decision about participation is taken. Patients who are not included in the study will continue in the usual rehabilitation program. Information on fulfillment of the in- and exclusion criteria, and stated reasons for non-participation will be recorded. Patients who need time to make a final decision whether to participate in the study or not, should return a completed consent form within two days of the clinical examination.

### Randomization

Randomization will be performed by staff at the admitting hospital using specialized computer software. To ensure balance between different patient groups, the randomization will be stratified according to gender, age (four groups), MS type (three groups), duration of diagnosis (five groups), EDSS score (three groups), and whether or not the patient is admitted to the hospital for the first time (two groups).

### Preparation day

The preparation day will take place seven days prior to the scheduled hospitalization. The overall purpose of the rehabilitation program will be explained and the individual areas for rehabilitation efforts will be defined in a collaboration between the patient and an appointed supervisor who serves as both the patient’s coach and as an 'orchestra conductor' for the rehabilitation team during the entire hospitalization. Prior to this preparation day, the patient will complete a FAMS form [16], a questionnaire on diet, smoking, alcohol and exercise, and indicate which of five focus areas is most important for him/her:

Energy level, including fatigue, scheduling, breaks and structure

Cognitive function, including memory, concentration and insight

Physical function, including walking, balance, endurance, strength and mobility

Psychological well-being, including strengthening coping mechanism, confidence, self-care, cognition and adjustment processes

Personal needs, including transferring, urination, toilet visits, bathing and medication.

The patient will also complete Form one in MYCaW [17,18]. The conversation follows clinical guidelines for target setting content and includes COPM [19-22] as identification and qualification of the decision basis for the objective. The conversation leads to identification of the primary goal within the five main areas (see above) and specific subsidiary goals and described cf. International Classification of Functioning, Disability and Health (ICF) classification of activity or participation level, supplemented by specific milestones [23].

### Four-week hospitalization

A hospitalization period of 20 days is organized as four weeks of continuous hospitalization. A team of relevant professionals is composed based on the assessment of the patient's needs and may include neuropsychologist, clinical psychologist, occupational therapist, physiotherapist, nutritional therapist or dietitian, nurse, healthcare assistant, nursing assistant, social worker. The neurologist will carry out the primary standard neurological examination and serve as consultant for the patient and supervisor for the team. Symptomatic drug therapy is organized or administered after the usual guidelines and the neurologist’s judgment.

The patient’s supervisor is responsible for the content of the patient's program and should oversee that it contributes to the work of the team and patient, works towards the agreed objectives and milestones and that the necessary adjustments are made during hospitalization. The supervisor and the patient continuously evaluate the program, for example by weekly conversations, and at discharge. According to patients’ wish, relatives and other team members may participate in one or more of the conversations.

During the rehabilitation period process data are collected on selected specific rehabilitation interventions, their nature, number, duration and medication.

### Outcome measures

Patient outcome will be measured by a variety of standardized quality of life (QoL), mastery and individual goal-related endpoints. A combination providing the basis for analyzing the complexity of MS and outcomes of a personalized rehabilitation.

### Standard endpoints and associated measurement instruments

Disease-specific quality of life: Multiple Sclerosis Impact Scale version 2 (MSIS-29) [24,25] and Functional Assessment of Multiple Sclerosis (FAMS) [16,26]

Mastery: Health Education Impact Questionnaire (heiQ) [27]

Generic Quality of Life: EQ-5D [28-30] and 15D [31]

Expanded Disability Status Scale score (EDSS) [11]

Fatigue: Modified Fatigue Impact Scale (MFIS) ) [32,33] (also used as individual endpoint)

Sleep: Epworth Sleepness Scale (ESS) [34], Pittsburghs Sleep Quality Index (PSQI) [35-38] (also used as individual endpoint)

Self-assessment of the severity of two main self-selected problems for which the patient seeks help and general feeling of well-being (MYCaW) [17,18]

Resource consumption and costs for patients and their relatives, and for the rest of health care service

### Individual goal-related endpoints and associated measurement instruments

After randomization, each participant will attend a preparation day, when individual goals and endpoints for the rehabilitation program will be determined according to the following areas:

Energy level: Modified Fatigue Impact Scale (MFIS) [32], Epworth Sleepness Scale (ESS) [34], Pittsburghs Sleep Quality Index (PSQI) [35-38]

Cognitive function: Modified Fatigue Impact Scale (MFIS) [32]

Physical function: Six-minute walk test (6MWT) [39-41], Multiple Sclerosis Walking Scale [42-45], Dynamic Gait Index (DGI) [46,47], Five Times Sit-To-Stand Test (5SST) [48,49], 9-Hole Peg Test (9-HPT) [50-52] and Six Spot Step Test (SSST) [53,54]

Psychological well-being and: Multiple Sclerosis Self-Efficacy Scale (MSSE) [55-57] and Coping Self-efficacy Scale (CSE) [58-60]

Personal needs: Barthel-100 index [12-14,61]

These questionnaires and physical tests are selected to capture changes in individual goals.

The Mastery (heiQ) and QoL (FAMS) are the only tests to be performed also one month after discharge in order to assess any changes in mastery and QoL shortly after returning home.

The individually chosen tests will be supplemented by Assessment of Motor and Process Skills (AMPS) [62,63] that include measurements of efficiency, safety, autonomy and effort in motor and process skills. This is relevant for measurements of changes in all five focus areas.

Physical tests will be performed at the clinical examination prior to inclusion, at the preparation day, at discharge and at 6 and 12 months follow-up. If the patient has received an aid during the rehabilitation program, the discharge tests will be performed both with and without aids. For practical reasons and to avoid patient burden, it is probably not possible to conduct all the physical tests for a participant during one morning session. Some tests may thus be delayed (after a rest or the following day). Such an approach is not expected to influence the validity of the test results [64]. However as patients are typically tested in the afternoon at inclusion, they will also be retested in the afternoon at discharge to avoid any effects of time differences.

### Data collection

The data collection is planned as outlined in Table 1. Measurement times for the early admission group include baseline (Time A1), preparation day (Time A2), day of discharge (Time A3), one-month follow-up after discharge (Time A4), six-month follow-up after baseline (Time A5) and twelve-month follow-up after baseline (Time A6).

**Table 1 T1:** Time points for data collection during the study

	**Intervention (early admission)**	**Control (usual admission)**
Baseline	Time A1	Time B1
6 months after baseline		Time B2
Preparation day	Time A2	Time B3
Day of discharge	Time A3	Time B4
1 months after discharge	Time A4	Time B5
6 months after baseline	Time A5	
12 months after baseline	Time A6	Time B6

Similarly, the six measurement times for the usual admission group are baseline (Time B1), six-month follow-up after baseline (Time B2 - acts as the control measurement – no intervention), the preparation day (Time B3), day of discharge (Time B4), one-month follow-up after discharge (Time B5) and twelve-month follow-up after baseline (Time B6).

Collection of patient-reported outcomes will mainly be based on online versions of the questionnaires, but questionnaires administered at the preparation day and at discharge will be in paper versions (Table 2). Patients who have completed the consent form will be assigned a unique study identification number and a login code to the web-based data collection system SurveyXact (http://www.surveyXact.dk). This password provides access to the questionnaire to be answered in accordance with the measurement time.

**Table 2 T2:** Questionnaires and assessments in the study

**Instruments**	**A1/B1**	**B2**	**A2/B3**	**A3/B4**	**A4/B5**	**A5**	**A6/B6**
	**(baseline)**	**(6 mths after baseline)**	**(preparation day)**	**(day of discharge)**	**(1 mths after discharge)**	**(6 mths after baseline)**	**(12 mths after baseline)**
Personal characteristics							
Initial assessments	x						
Subsequent assessments		x				x	x
Standard outcomes							
MSIS-29	x	x		x		x	x
FAMS	x	x		x	x	x	x
heiQ	x	x			x	x	x
EQ-VAS	x	x		x		x	x
EQ-5D/15D	x	x				x	x
EDSS	x	x				x	x
MFIS	x	x				x	x
ESS/PSQ	x	x				x	x
MYCaW			x	x		x	x
Walking distance test	x	x				x	x
Goal-related outcomes							
Energy-level			x	x		x	x
Cognitive function			x	x		x	x
Physical function			x	x		x	x
Psychological well-being			x	x		x	x
Personal needs			x	x		x	x
Motor and Process Skills			x	x		x	x
Services used during admission							
Use of different services				x			

### Pilot study for data collection

In November 2011 a pilot study was conducted to test and adjust the screening and randomization processes, and to test the online survey facility. Data were collected for 8 patients in accordance with the protocol for the two groups. This pilot study identified a number of practical challenges that were addressed in the final study protocol. The target group was expanded from only patients who were referred for the first time to also include patients who had previously been admitted to the hospitals. The inclusion criteria were tightened to require that participants should be able to respond to the computerized questionnaires. A maximum age of 65 years and an additional exclusion criterion regarding other illnesses that could impede participation in the study were introduced. In addition, the screening for depression was changed to be part of the clinical assessment rather than being based on self-assessment.

### Register and economic data

In addition to data from questionnaires, data from routine administrative health registries will be obtained from the Sclerosis Hospitals, the national patient registry and the primary care registry (through the National Board of Health’s research service) and the registry of primary care prescription medicine. Data available in these registries include records of actual resource consumption (number of hospitalizations, outpatient visits and consultations) and costs in terms of service fees, fees paid to health care providers and pharmacy retail prices (AUP). Data on vital status will be obtained from the national mortality registry. These data will be obtained for the years 2010–14, i.e. for the two years prior to baseline and up to the 12 months of follow-up.

### Data analysis

#### Sample size calculation

Determination of the required sample size is based on known data from the previous FAMS study [8,26]. The FAMS total score ranges from 0-170 and the average score at referral was 103 (SD 27). Assuming that a 5% score change indicates a clinically significant change, then the mean score should change to more than 108 i.e. that a clinically significant change requires a 5-point change.

To test a 5-point difference between two groups with 5% statistical significance (alpha) and 90% power (beta), the calculated required number of participants in each group is 613 people. With 80% power the required number of participants is reduced to 458.

If we want to test a 10-point difference, there needs to be 154 people (assuming 90% power) or 115 people (80% power).

The current study participants are expected to be a more homogeneous group than in the previous study, thus the variation in FAMS score is likely to be reduced. If the standard deviation is assumed to be 20 (instead of 27), then 252 patients will be needed in each group to identify a 5% difference with 80% power.

Taking into account correlation between repeated measurements for the same individual and assuming that the correlation between two subsequent measurements is 0.8, a 5-point difference could be identified with 160 participants (90% power) or 120 participants (80% power) in each group.

Based on these assessments a reasonable sample size is considered to be around 200 participants in each of the two groups. The Sclerosis Hospitals expects to admit 1,200 people with multiple sclerosis in the period March 2012 through June 2013. An unknown number will be either excluded from the study or will decline to participate in the study. If an insufficient number of patients has been recruited at the end of the planned inclusion period, a (short) extension of the inclusion period will be possible.

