### Comparative analysis

The following comparative analysis will be conducted:

Difference from Time A1 to Time A5 for intervention group compared with the difference from Time B1 to Time B2 for control group (i.e. difference in outcomes for rehabilitation vs. no rehabilitation at 6-month follow-up)

Difference between Time A1 and Time B1 (i.e. difference between intervention and control group at baseline)

Difference between Time A1 and Times A5 and A6 (i.e. baseline vs. 6- and 12-month follow-up for intervention group)

Difference between Time B3 and Time B6 for control group (i.e. admission vs. 12-month follow-up).

Difference between A2 and A3 for intervention group (pre- vs. post-hospital rehabilitation)

Difference between B3 and B4 for control group (pre- vs. post-hospital rehabilitation).

Difference between Time A1 and Time A4 for intervention group A (baseline vs. one month after hospital rehabilitation)

Difference between Time B3 and Time B5 for control group (pre- vs. one month after hospital rehabilitation)

Changes in Mastery (heiQ) over time: Times A1, A4, A5 and A6 for intervention group compared with Times B1, B2, B5 and B6 for control group

Subgroup analyses will be performed on the individual focus areas, based on data from participants who have completed the goal-related questionnaires.

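### The 160/120-per-group figures do not follow from either stated SD for the one-follow-up comparison the trial makes; restate them and give the power of 200 per group

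*Protocol article*

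**What the plan says.** The Sample size calculation section of the protocol article works with the FAMS total score. It takes a mean of 103 and SD 27 from the previous study and says that "a clinically significant change requires a 5-point change". Without using repeated measurements, it gives 613 (90% power) or 458 (80%) per group for 5 points, and 154 or 115 for 10 points. It then expects a more homogeneous sample: "If the standard deviation is assumed to be 20 (instead of 27), then 252 patients will be needed in each group" at 80% power. The next step, "assuming that the correlation between two subsequent measurements is 0.8", leads to the statement that "a 5-point difference could be identified with 160 participants (90% power) or 120 participants (80% power) in each group". From all of this it concludes that "a reasonable sample size is considered to be around 200 participants in each of the two groups".

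The Methods and design section defines the programme effect as the between-group difference from baseline to six months. The Comparative analysis section puts this as "Difference from Time A1 to Time A5 for intervention group compared with the difference from Time B1 to Time B2 for control group". In the Data collection section, B2 is the control arm's measurement without intervention. Controls are admitted at about eight months, so their discharge, one-month and twelve-month values all follow treatment.

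**The concern.** A sample size with a stated power should be reproducible from the stated inputs for the comparison that the trial will make. This one is not, and it carries weight: of the calculations for a 5-point difference (613, 458, 252 and 160/120), only the last falls below 200. If it rests on a second follow-up that the between-arm comparison does not have, it overstates the power for the difference that the protocol itself calls clinically significant.

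**Working it through.** **Inputs.** From the Sample size calculation section: difference 5 points, alpha 5%, power 90% or 80%, SD 27 or 20, correlation r = 0.8. The section does not state sidedness; two-sided is used because it reproduces the simple figures. From the Comparative analysis section: one baseline and one follow-up per arm. Assumption: the same r between every pair of measurements.

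**Formula.** n per group = 2 × (1.960 + z)² × f × SD² / 5², rounded up, with z = 1.2816 (90%) or 0.8416 (80%). The squared sums are 10.507 and 7.849. The factor f is:
- no repeated measurements: f = 1
- baseline-adjusted, mean of k follow-ups: f = (1 + (k − 1)r)/k − r²
- change from baseline, mean of k follow-ups: f = (1 + (k − 1)r)/k + 1 − 2r

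**Simple figures (f = 1).** SD 27: 2 × 10.507 × 729/25 = 612.8, so 613; with 7.849 it is 457.8, so 458. For 10 points, dividing by 4 gives 154 and 115. SD 20 at 80%: 2 × 7.849 × 400/25 = 251.2, so 252. All agree with the article.

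**A source for 160/120.** SD 27, baseline-adjusted, two follow-ups: f = 1.8/2 − 0.64 = 0.26. Then 612.8 × 0.26 = 159.3 and 457.8 × 0.26 = 119.0 (119.01 unrounded). Rounded up, these are 160 and 120, an exact match.

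**One baseline and one follow-up.** Here f = 1 − 0.64 = 0.36 (baseline-adjusted) or 2 − 1.6 = 0.40 (change score).

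| SD | Analysis | n, 90% power | n, 80% power |
|---|---|---|---|
| 27 | baseline-adjusted | 220.6 → 221 | 164.8 → 165 |
| 27 | change score | 245.1 → 246 | 183.1 → 184 |
| 20 | baseline-adjusted | 121.05 → 122 | 90.4 → 91 |
| 20 | change score | 134.5 → 135 | 100.5 → 101 |

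No row gives 160/120.

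**Power with one follow-up.** Power = Φ(5 / (SD × √(2f/n)) − 1.960). Example: SD 27, f = 0.36, n = 160 gives an effective SD of 16.2 and a standard error of 1.811, so Φ(2.761 − 1.960) = 0.788.

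| n per group | SD 27, adjusted | SD 27, change | SD 20, adjusted | SD 20, change |
|---|---|---|---|---|
| 120 | 66.7% | 62.1% | 89.8% | 86.5% |
| 160 | 78.8% | 74.5% | 96.1% | 94.2% |
| 200 | 87.0% | 83.4% | 98.6% | 97.7% |

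If 20% of 200 are lost (assumption), 160 are analysed and the 160 row applies. At SD 27, power at 200 stays at 80% or more up to a loss of 1 − 165/200 = 17.5% (adjusted) or 1 − 184/200 = 8% (change score).

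**The case against.** The strongest objection is that the shortfall depends on an SD that the section does not attach to this step. The paragraph just before introduces SD 20 as the likelier value, and at SD 20 the figures err on the safe side. This stands, and it limits the point: the power claim fails at SD 27 but not at SD 20. It does not rescue 160/120 as a calculation, since SD 20 with one follow-up does not give those numbers either.

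The two-follow-up origin is also reconstructed, not stated. A reader might infer that it is the only possible source, and the documents do not support that. A three-follow-up change score at SD 27 comes close (164/123). So does SD 20 with an unstated dropout allowance (change score, 15%: 159/119). One baseline-adjusted follow-up at SD 23, which the section does not state, gives 160.1/119.6.

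The longitudinal random-effects models planned under Descriptive analysis could use more of the data, and the Preparation day section mentions a FAMS form that for controls would be a second untreated value. But Table 2 does not mark FAMS at that visit, and the between-arm comparison does not use it.

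Finally, a reader might infer that 200 was claimed to give 90% power with room for losses. The section attaches no power to 200 and calls it only reasonable. Nor does the article plan a between-arm average of six- and twelve-month values, so a loss of power from treated controls at month 12 cannot be charged to it.

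**Conclusion.** The point holds in limited form. As written, 160/120 cannot be obtained from either stated SD for the comparison of baseline with six months between arms. If SD 27 applies, the stated 90% and 80% are really about 79% and 67% (baseline-adjusted) or 75% and 62% (change score), an overstatement of 11 to 18 percentage points. If SD 20 applies, 160/120 is more than needed. These results assume a two-sided test, r = 0.8, a 5-point difference and complete data.

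It would go too far to conclude that the trial is underpowered. With complete data, the target of 200 exceeds 80% power at SD 27 under both analyses, though it misses 90%, and it is ample at SD 20.

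**What to change.** Replace 160/120 with the one-follow-up figures and name the SD and the analysis form beside each. At SD 27: 221 (90%) or 165 (80%) per group with baseline adjustment, 246 or 184 with change scores. At SD 20: 122 or 91, and 135 or 101. Keep the target of 200 and state its power with complete data: about 87% (baseline-adjusted) or 83% (change score) at SD 27, and 98–99% at SD 20. Add that at SD 27 power falls to about 79% or 75% if 20% are lost, marked as an assumption.

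The cost is wording only. The stated power at SD 27 becomes less favourable; no extra patients are needed.
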